#### Qualitative experience with MPOTA-WM

During interviews with research program participants, we will also explore individuals’ experiences with MPOTA-WM and solicit feedback on opportunities to improve the text messaging program.

#### Change in weight

We will evaluate change in weight from baseline to 12 months of follow-up among MPOTA-WM users. To account for potential differences between clinic and home scales, the first weight entered by text message will serve as participants’ baseline weight for remote weight monitoring and this will be compared with follow-up MPOTA-WM data.

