MPOTA-WM participants will be asked to self-weigh at least once per week and report their weight data via text message. Participants without access to a home scale will be provided with one by the study team. Participants will be asked to use the same scale throughout the duration of the study. Participants will self-select the day(s) of the week and time of the day to receive the following text message: ‘Hello, this is your Weight Navigation Program Research Team. What was your weight in pounds today? Reply STOP to opt out of receiving messages from our team’. The WNP team will receive inbox notifications based on the following parameters, which have been adapted from prior literature (Baer *et al*., 2020): (1) weight gain of ≥ 3 pounds at any point; (2) weight loss of varying thresholds (eg, 3%, 5%, and 10% body weight loss); (3) non-response to MPOTA for weight management messages for 14 days; and (4) participants’ ‘STOP’ responses, indicating that they are discontinuing their participation in the text messaging program. The research project manager will initiate tailored outreach; those losing weight, for example, will receive a supportive EHR portal message while those gaining weight will receive a phone call to discuss barriers to weight management, individuals’ preferences and needs, and other available weight management options, as detailed in the WNP encounter note. Communication will be documented in the EHR and patients’ primary care, WNP, and/or weight management subspecialty providers will be alerted, as appropriate.

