##### Change in survey measures

Research program participants will be asked to complete surveys at baseline, 6 months, and 12 months; we will determine changes in measures at 6 and 12 months compared to baseline. Survey measures include motivation to lose weight (Kullgren, 2016), perceived competence to lose weight (Williams *et al*., 1998), social support (Sarason *et al.*, 1987), and eating behaviors (de Lauzon *et al.*, 2004). At baseline, we will ask participants to report sociodemographic characteristics.

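### The text-based 12-month weight change has no value for participants who have sent STOP or are still silent at month 12; one home-scale weight question in the scheduled surveys would recover some of them

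*Protocol article*

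**What the plan says.** All references are to the protocol article.

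- **Outcome.** Under the remote-monitoring outcomes, *Change in weight* states: "We will evaluate change in weight from baseline to 12 months of follow-up among MPOTA-WM users". The baseline rule, meant to keep home-scale and clinic-scale weights apart, reads: "the first weight entered by text message will serve as participants’ baseline weight for remote weight monitoring and this will be compared with follow-up MPOTA-WM". *Quantitative data analysis* names the same source for the mean change in research participants, and presents it as an addition to the between-group comparisons.
- **Leaving the text programme.** *Intervention* sets an alert for "non-response to MPOTA for weight management messages for 14 days" and another for "participants’ ‘STOP’ responses, indicating that they are discontinuing their participation in the text messaging program". After an alert, "The research project manager will initiate tailored outreach". No step to obtain a missing weight is described. Participants are asked to keep to one scale for the whole study, and those without a scale are given one.
- **Surveys.** *Change in survey measures* states: "Research program participants will be asked to complete surveys at baseline, 6 months, and 12 months". The measures named are motivation, perceived competence, social support and eating behaviours, plus sociodemographic items at baseline. Weight is not among them. *Research retention* is defined by survey completion, not by texting.
- **Other weights.** Under *Clinical impact of the WNP*, *Change in weight* takes health-record weights for every WNP patient who completes a visit in the first year of operation and follows change for 12 months. *Quantitative data analysis* compares all WNP participants with the research participants on weight.

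**The concern.** The text channel is both the intervention being piloted and the only instrument for this outcome. A participant who leaves the intervention also leaves the outcome, although nothing in the article says that STOP ends study participation and the 12-month survey is still due. The 12-month change then describes those still texting at month 12.

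People who stop reporting their weight may well be doing worse than those who continue. That is a judgement, not a figure in the article. If it is right, the preliminary effectiveness of remote monitoring will look better than it is, and *Future directions* intends these data to inform a refined programme and a later large trial.

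This is a matter of what is collected. An analysis plan can choose a method for missing values, but it cannot supply a home-scale weight that nobody asked for.

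**Working it through.** **Is there a figure to reproduce?** No. The target of 30 in *Recruitment* comes without a power calculation, and no STOP rate, attrition rate or expected weight change is given. The check is therefore a trace of the weight sources, followed by an illustration on assumed values.

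**Step 1: which weights exist at month 12, by texting status?**

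| Status at month 12 | Text-based outcome | Health-record weight | 12-month survey |
|---|---|---|---|
| Still texting | yes | if weighed in clinic near 12 months | due, no weight item listed |
| Silent for a time, then back after outreach | yes | same | same |
| Still silent despite outreach | no | same | same |
| Sent STOP | no | same | same |

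The health-record column applies to those who attended their WNP visit. The gap is confined to the last two rows and to the text-based outcome.

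**Step 2: size of the possible bias.** Assume that all 30 have a first texted weight and that the mean is taken over those with a 12-month text. Let *m* be the share without a 12-month text, *R* the mean percentage loss in reporters, *N* the mean percentage loss in non-reporters, and *d* = *R* − *N*.

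- Whole-group mean loss = (1 − *m*)*R* + *mN*
- Overstatement = *R* − [(1 − *m*)*R* + *mN*] = *m* × *d*
- Number left, *k* = 30(1 − *m*); standard-error inflation = √(30/*k*)

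Both *m* and *d* are assumptions.

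| *m* | *k* | SE inflation | Overstatement, *d* = 2 | Overstatement, *d* = 5 |
|---|---|---|---|---|
| 10% | 27 | 1.05 | 0.2 points | 0.5 points |
| 20% | 24 | 1.12 | 0.4 | 1.0 |
| 30% | 21 | 1.20 | 0.6 | 1.5 |
| 40% | 18 | 1.29 | 0.8 | 2.0 |

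One case in full: if persisting texters lose 5%, the others lose 1% and *m* = 40%, the whole group loses 0.6 × 5 + 0.4 × 1 = 3.4%, against 5.0% in the 18 reporters. The difference, 1.6 points, equals 0.4 × 4.

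**Step 3: what a survey item could recover.** If a share *r* of the non-texters answer the survey, the share still missing falls from *m* to *m*(1 − *r*). If those who answer resemble the other non-texters, the overstatement becomes *md*(1 − *m*)(1 − *r*) / [1 − *m*(1 − *r*)]. This is zero when *r* = 1 and the full *md* when *r* = 0. The article gives no basis for a value of *r*.

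**The case against.** A reader might infer that people who stop texting have no 12-month weight at all. The article does not support that. Research participants who attend their WNP visit are WNP patients, so their health-record weights are abstracted whether or not they text, and those weights enter a planned comparison. Nor does the scale problem invalidate those weights: a change from one health-record weight to another mixes no home and clinic scales. What the scale problem rules out is using a clinic weight in place of a missing text. The remaining limit is that a clinic weight near 12 months is opportunistic.

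A reader might also take 14 days of silence as permanent loss. It is a trigger for outreach, and texting can resume. Only STOP ends it.

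Three further objections deserve weight.

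- **The article is condensed.** Its list of survey measures is introduced as what they include, so a weight item may exist. Even then, the outcome as defined draws on texted weights only, and a survey weight would not enter it.
- **No analysis restricted to month-12 reporters is declared.** This is true, and the arithmetic above assumes one. Using the last texted weight instead would keep more people, but it would not be a 12-month value for those who stopped earlier.
- **The outcome is modest.** It is openly limited to users of the text programme, uptake and engagement are reported with it, and the primary outcomes are feasibility and acceptability. This limits the consequence but does not remove the gap.

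**Conclusion.** The point holds in a limited form. The text-based 12-month outcome has no value for participants who have sent STOP or remain silent at month 12, and their only other planned weight is a clinic-scale one that may not exist near that date. If stopping is related to poor weight loss, the text-based mean overstates loss.

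The direction rests on that judgement, and the size rests wholly on assumption: about 0.2 to 2.0 percentage points for 10% to 40% lost and a 2 to 5 point difference, before any recovery. The article states nothing wrongly here and contradicts nothing. This is a cheap improvement to a secondary descriptive measure, and it does not touch the primary outcomes.

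**What to change.** - Add one item to the existing 6- and 12-month surveys: today's weight in pounds, on the same home scale used for texting. Ask it of every research participant, including those who sent STOP.
- Use the survey weight as the 6- or 12-month remote weight when no text falls in the window.
- Report the change in all participants with a first texted weight beside the change in persisting texters, with the number contributing to each.
- Show the change between health-record weights in research participants as a check.

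The cost is one survey question and a short change to the outcome definition. No visit, staff or equipment is added, because every participant already has or is given a scale. There are two downsides. The weight stays self-reported, as the texts are. And it is recovered only from non-texters who still complete the survey; those who stop texting may skip the survey too, so some informative loss can remain.

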### Study design

This is a clinical quality improvement project with an embedded single-arm pilot study. Specifically, patients with obesity who desire to lose weight will be referred by their PCP to the WNP. Patients scheduled for a WNP appointment will be offered the opportunity to participate in research; we will aim to recruit 30 participants to the research arm of the study Research activities include (1) surveys at 0, 6, and 12 months; (2) optional semi-structured interview participation at 0 and 6 months; and (3) use of a text messaging program for remote weight monitoring.

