### Recruitment

Patients will be referred to the WNP by PCPs. All patients scheduled for a WNP appointment will be eligible for participation in a single-arm, 12-month pilot study. We anticipate that the Weight Navigator will see approximately 4 patients per 4-h clinic session once per week. Accounting for vacations, holidays, and canceled appointments, we estimate that the Weight Navigator will see approximately 150 patients during the first year of the program.

All patients scheduled for a WNP appointment will be eligible for participation in a single-arm, 12-month pilot research study. A research project manager will contact scheduled patients by telephone at least 5 days prior to their appointment date to invite them to participate in research and describe the study processes. Individuals who desire to participate in research will complete an online informed consent document and the baseline survey prior to the WNP appointment using the RedCap survey platform (REDCap, n.d.). Recruitment will continue until we reach our target of 30 participants.

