### Outcome measures

We have 4 outcome categories: (1) feasibility and acceptability of the WNP; (2) clinical impact of the WNP; (3) feasibility, acceptability, and preliminary effectiveness of adding remote weight monitoring by text messaging to the WNP; and (4) feasibility and acceptability of research processes including recruitment and data collection.

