### Data analyses

#### Quantitative data analysis

Measures of central tendency (eg, proportions, means, standard deviations) will be used for all descriptive analyses. We will calculate mean 3-month and 6-month weight changes from baseline. We will also calculate the number of participants that achieve ≥5% body weight loss at 6 and 12 months. We will compare between-group changes (ie, all WNP participants versus WNP research participants and all WNP participants versus matched cohort) in weight using a difference-in-difference analytic approach. Among WNP research participants, we will also calculate mean weight change based on MPOTA-WM data. We will conduct all analyses using Stata 15.

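### The weight outcome for adding remote monitoring has no comparator, and the one planned contrast that could supply it is not tied to that question and uses overlapping groups

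*Protocol article*

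**What the plan says.** The Outcome measures section of the protocol article lists as its third category "feasibility, acceptability, and preliminary effectiveness of adding remote weight monitoring by text messaging to the WNP". Under that heading, the Change in weight paragraph gives the only weight outcome: "We will evaluate change in weight from baseline to 12 months of follow-up among MPOTA-WM users". Its data source is the text messages, since "the first weight entered by text message will serve as participants’ baseline weight for remote weight monitoring" and later texted weights are compared with it.

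The monitored patients are drawn from the programme: "Patients scheduled for a WNP appointment will be offered the opportunity to participate in research". The Study design section is open about the design: "This is a clinical quality improvement project with an embedded single-arm pilot study". On numbers, the Recruitment section says "Recruitment will continue until we reach our target of 30 participants" and "we estimate that the Weight Navigator will see approximately 150 patients during the first year of the program".

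The Quantitative data analysis section plans a difference-in-difference analysis of weight with two contrasts: all WNP participants against WNP research participants, and all WNP participants against the matched cohort. It then adds: "Among WNP research participants, we will also calculate mean weight change based on MPOTA-WM data". Separately, the section on the clinical impact of the WNP provides for EHR weights on every WNP patient who completes a visit in the first 12 months of operation.

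**The concern.** The category asks an incremental question: what does monitoring contribute on top of the WNP? The weight outcome defined for it is the total change in patients offered both. Apart from any who consent but miss the appointment, each of them also has the hour-long Navigator visit, the treatment referrals and possibly an anti-obesity medication recommendation. No feature of the measure separates the two sources of change.

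If the WNP works, the outcome will tend to show loss whether monitoring helps, does nothing or mildly hinders. The pilot's results are meant to refine the programme before a larger trial. The article also notes that the text-message outreach depends on research funding. Crediting monitoring with loss that the WNP produced could carry that component forward without evidence that it adds anything.

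**Working it through.** The protocol states no test, SD, effect size or power for this outcome, so there is no figure of its own to reproduce.

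**Inputs from the protocol article (Recruitment):** 30 research participants; about 150 WNP patients in year 1; hence about 150 − 30 = 120 unmonitored.

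**Assumptions, not in the protocol:** all 30 are among the 150; SD of 12-month weight change 5, 7 or 9 percentage points, equal in both groups; no dropout.

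**Step 1. What the texted-weight change estimates.** Write W for the mean change due to the WNP and other background influences, and A for the added effect of monitoring. The measure estimates W + A. With A = 0 it estimates W, which is a loss if the WNP works. A same-source comparator cannot be built, because unmonitored patients have no texted weights.

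**Step 2. Illustration of step 1.** Suppose someone applied a paired two-sided 5% test to 30 patients with A = 0. The noncentrality is (mean loss / SD) × √30. The chance of a significant loss is:

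| Loss from WNP alone | SD 5 | SD 7 | SD 9 |
|---|---|---|---|
| 3 points | 89% | 62% | 42% |
| 4 points | 99% | 86% | 65% |
| 5 points | >99% | 97% | 84% |

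These are not error rates of a planned analysis.

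**Step 3. The planned contrast with overlapping groups.** Let M and U be the mean changes in monitored and unmonitored WNP patients. The mean of all WNP patients is (30/150)M + (120/150)U = 0.2M + 0.8U. The contrast is therefore M − (0.2M + 0.8U) = 0.8(M − U), and a true difference of 3.0 points appears as 0.8 × 3.0 = 2.4. The factor is 1 − 30/N, so it moves with the clinic total: 0.70 if N = 100, 0.85 if N = 200.

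The standard error is affected too. Treating the two groups as independent gives SD × √(1/30 + 1/150) = 0.200 × SD. The correct value for the overlapping contrast is 0.8 × SD × √(1/30 + 1/120) = 0.8 × 0.204 × SD = 0.163 × SD. A naive analysis would thus pair a shrunken estimate with too large a standard error.

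**Step 4. Precision without overlap.** For 30 against 120, the 95% half-width is 1.96 × SD × √(1/30 + 1/120) = 1.96 × 0.204 × SD. This gives 2.0, 2.8 and 3.6 percentage points for SD 5, 7 and 9.

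**The case against.** The strongest reply is that the comparison already exists. The planned contrast of all WNP participants with research participants sets monitored patients against WNP patients in general. If monitoring and the other research activities add nothing, and volunteers do not differ from other patients, its expected value is zero. A condensed article may define measures in one section and comparisons in another, so a missing cross-reference could be called editorial. The texted-weight mean is also only to be calculated, with no test or decision attached. The primary outcomes are feasibility and acceptability, and effectiveness is called preliminary.

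Much of this stands. A reader might infer that the plan as a whole will make monitoring look effective even if it adds nothing. The documents do not support that: the difference-in-difference contrast is there, and loss in the texted weights depends on the WNP itself working, which the protocol hypothesises without giving a size. Nor should a reader take the percentages in step 2 as the plan's false-positive rate, or a 5-point mean loss as the programme's target. The protocol uses 5% as a threshold for individual patients.

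The reply does not remove the defect. By contrast, the section on the clinical impact of the WNP names its matched-cohort comparison within the outcome itself. The monitoring outcome names none, and the analysis section lists the texted-weight mean separately. The contrast that could answer the question states neither its weight source nor its time point, and its groups overlap.

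**Conclusion.** The point holds, within limits. The texted-weight change cannot measure the preliminary effectiveness of adding monitoring. The planned contrast comes close, but is not tied to that category and shows about 80% of any true difference under the protocol's own figures of 30 and 150. That factor assumes all 30 fall within the 150. The structural conclusion in step 1 needs no assumed SD or effect size.

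Non-overlapping groups will not make the comparison causal. Research participants must be willing to text their weights and accept outreach, and they also complete surveys and may be interviewed. A difference could therefore reflect selection or those other activities. The pilot's small size excuses a wide interval, but not an outcome that answers a different question from the one its heading poses.

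**What to change.** In the Change in weight paragraph under remote monitoring, and in the Quantitative data analysis section:

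- Define the effectiveness measure for this category as the difference in 12-month EHR weight change between research (monitored) and non-research (unmonitored) WNP patients, with no patient on both sides.
- Use EHR weights in both groups.
- Adjust for baseline weight and other baseline characteristics available in the EHR.
- Report the estimate with its confidence interval as exploratory, and state that participants are volunteers.
- Keep the texted-weight change as a description of the WNP and monitoring combined, and say that it is not evidence on what monitoring adds.

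The cost is the rewording of one outcome and one analysis sentence, plus one regression on weights already being abstracted. The downside is a wide, non-randomised interval, as computed in step 4.

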### Feasibility, acceptability, and preliminary effectiveness of adding remote weight monitoring by text messaging to the WNP

#### MPOTA-WM uptake

Determined by the number of individuals who consent to research divided by the number of individuals who self-report at least 1 weight measure by text message.

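### The remote-monitoring baseline is the first texted weight with no tie to the WNP visit, so weight change before a late first text drops out of the 12-month texted result

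*Protocol article*

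**What the plan says.** The Change in weight paragraph under remote weight monitoring defines the measure: "We will evaluate change in weight from baseline to 12 months of follow-up among MPOTA-WM users". It fixes the starting point: "the first weight entered by text message will serve as participants’ baseline weight". The only reason it gives is about equipment: "To account for potential differences between clinic and home scales".

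Other sections bear on when that first text can arrive:

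- **Recruitment.** Those who agree to take part "will complete an online informed consent document and the baseline survey prior to the WNP appointment". A texted weight is not among the things due before the visit.
- **Intervention.** Initial treatment referrals are made in connection with the WNP visit. Participants weigh themselves at least weekly and choose when the text prompt reaches them; no start date for texting is given. On equipment: "Participants without access to a home scale will be provided with one by the study team", with no date for supply. The team is notified after 14 days without a reply.
- **MPOTA-WM uptake.** The definition uses "the number of individuals who self-report at least 1 weight measure by text message", with no time limit.
- **Clinical impact of the WNP, Change in weight.** A separate outcome uses EHR weights over the 12 months after the WNP appointment.
- **Quantitative data analysis.** Mean weight change from the texted data is to be calculated for the research participants.

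**The concern.** A baseline for change after treatment should be taken at, or close to, the moment treatment starts. Here it is taken whenever the participant first replies. Someone who replies before the visit has a pre-treatment baseline. Someone who replies some weeks afterwards has a baseline that may already include part of the response.

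Two things follow. The measured change depends on promptness of engagement, which is itself something the pilot studies through its uptake and engagement measures. And the texted and EHR results can cover different periods for the same person, so a gap between them could reflect timing, scales or both.

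Future directions says that the pilot data will be used to refine the program ahead of a larger trial. A home-scale weight not collected before treatment cannot be recovered later.

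**Working it through.** The article states no figure for this measure, so there is none to reproduce. The check has four steps.

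**1. Is the first text dated anywhere?** Consent and the baseline survey are placed before the visit; the first text is not. The 14-day notice alerts the team but neither caps nor resets the baseline. Scale supply and uptake carry no time limit. So no section ties the baseline to the visit.

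**2. What does the rule measure?** Write W for weight.

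measured change = W(12 months) − W(first text) = [W(12 months) − W(visit)] − [W(first text) − W(visit)]

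The second bracket is the change before the first text, and it drops out in full. If weight fell in that gap, loss is understated. If weight rose, loss is overstated. If the first text is sent at the visit, the bracket is zero.

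The article does not say whether 12 months runs from the visit or from the first text. With a first text at week 8, counting from the visit covers 52 − 8 = 44 weeks. Counting from the first text covers weeks 8 to 60 after the visit. The early change is lost either way.

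**3. Size for one late starter.** Assumptions, none from the article: 100 kg at the visit, a true 12-month loss of 5%, and loss beginning at the visit. The loss is either linear or front-loaded (exponential, 12-week time constant).

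- Linear loss by week w: 5 × w/52
- Front-loaded loss by week w: 5 × (1 − e^(−w/12)) / (1 − e^(−52/12))
- Measured loss: 100 × (W(first text) − 95) / W(first text)

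| First text | Hidden, linear (kg) | Measured, linear | Hidden, front-loaded (kg) | Measured, front-loaded |
|---|---|---|---|---|
| Week 0 | 0.00 | 5.0% | 0.00 | 5.0% |
| Week 2 | 0.19 | 4.8% | 0.78 | 4.3% |
| Week 4 | 0.38 | 4.6% | 1.44 | 3.6% |
| Week 12 | 1.15 | 3.9% | 3.20 | 1.9% |

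**4. Size for the group.** Only late starters contribute. With k late starters among the 30 planned participants, each losing h percentage points of measured loss, the mean is understated by (k/30) × h.

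- k = 3: 3/30 × 1 = 0.1 points; 3/30 × 3 = 0.3 points
- k = 9: 9/30 × 1 = 0.3 points; 9/30 × 3 = 0.9 points

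The values of k and h are assumptions. The article gives neither a distribution of delays nor a weight trajectory.

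**The case against.** **Windows are detail that an article leaves out.** This is right about windows: their absence alone would be no finding. But the article itself chooses the baseline and gives its reason, and the chosen baseline is an event with no anchor. The comment is on that stated rule.

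**Starting the clock when monitoring starts suits the question.** The measure belongs to the outcome category on adding texting to the WNP, and loss before the first text is not an effect of texting. This is a coherent reading. It does not settle the matter, because the article justifies the rule by scale differences, not by the start of monitoring, and leaves the origin of the 12 months open. Under this reading too, participants would enter at different stages of treatment.

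**Scale differences are a real problem.** They are, and a single home scale throughout is sound. That supports where the baseline is measured, not leaving it undated.

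**Long delays may be rare.** Consent precedes the visit, prompts are at least weekly and silence is flagged, so some first texts may come before treatment. Referrals made around the visit also need not produce weight loss at once. All of this stands, and the number affected cannot be known from the article.

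**A stronger reading is tempting: that the share reaching 5% loss falls sharply.** With a mean loss of 5% and an SD of 6.5% (both assumed), taking 1 or 2 points off the mean lowers that share from 50% to 43.9% or 37.9%. The document does not support this. The calculation shifts every participant, although only late starters are affected: if 3 of 30 each lost 4 points, the mean would move 3/30 × 4 = 0.4 points and the same model gives about 47.5%. More basically, the 5% outcome is not clearly based on texted weights. The clinical-impact section attaches it to EHR data, and the analysis section names no source. No claim about that share should be made.

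**Conclusion.** The point holds within limits. As written, the baseline for the texted 12-month change is not anchored to the WNP visit, and for anyone whose first text follows the start of treatment, the weight change before it is excluded. That follows from the definition and needs no assumption about size.

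The size does need assumptions. With 3 to 9 late starters among 30, each losing 1 to 3 points, the mean is understated by about 0.1 to 0.9 percentage points; with no late starters there is no effect. The direction assumes that weight falls before the first text.

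The reach is narrow: one preliminary-effectiveness measure in about 30 people, in a pilot whose primary outcomes are feasibility and acceptability. A reader might infer that early loss disappears from the study altogether. It does not, because the EHR outcome is counted from the visit and neither it nor the matched-cohort comparison uses this baseline. The change is worth making because it is cheap.

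**What to change.** - Send the first weight prompt between consent and the WNP appointment, and supply any study scale by then.
- Define the remote baseline as the home-scale weight closest to the visit within a short window stated in advance. This keeps the single-scale rationale.
- Count the 12 months from the visit date, in line with the EHR outcome.
- Report the gap from visit to first text for all users.
- For participants with no home weight in the window, show the paired EHR weight change as a separate or sensitivity analysis. Do not mix it into the home-scale mean, which would bring back the scale difference that the rule was meant to remove.

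The cost is one timing rule in the texting set-up and a sentence or two in the analysis section. Consent already precedes the visit, so no new contact point is needed. The downside is that a few late starters leave the main home-scale analysis.
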